### **3.5.2 Primary outcome: definition and measurement**

The primary outcome will be the cumulative incidence of persistent HPV 16 or HPV 18 infections. The ultimate goal of HPV vaccination is to reduce cervical cancer's incidence and mortality. However, these reductions are only expected in 30, maybe 40 years. It is not desirable to wait that long before evaluating and if necessary adjusting the vaccination program. Therefore persistent infection is the surrogate outcome preferred by many organisations (e.g. WHO) when decisions on efficacy have to be taken in a relatively short time (10 years)(64,65). A persistent infection predicts the risk of precancer very well and is relatively easy to measure and replicate.

A persistent infection will be defined as the presence of HPV 16 or HPV 18 DNA in 2 specimens of vaginal self-samples over 2 consecutive samplings. The samples will be collected every 6 months. Self-sampling is done with a swab inserted in the vagina then stored in an empty vial, before being sent through postal mail. This process has been successfully used by various teams in similarly aged populations(66).

In this definition of persistent infection, we will accept 2 consecutive samples performed at a minimum of 5-month interval and a maximum of 15-month interval. Two-step HPV DNA identification will be performed to minimize the costs. First, a generic test will be performed in order to check if HPV DNA is present. Then a Linear Array test will be performed on positive samples in order to identify the type(s) of HPV. Each type will be counted separately.

More precisely: a dry swab collected from each participant will be eluted in TE buffer. Obtained Cells are lysed (proteinase K 200ug, Tween 20 0,8%, incubated 90 min 65°C) and used as is for amplification. If lysed sample doesn't amplify, DNA is purified using the Master pure™ protocol (Epicentre, Madison, WI)(67–69). The DNA from the samples will first be submitted to an amplification protocol and generic detection using non-radioactive markers validated by our team(70,71). The DNA of the HPV present in the samples will be amplified by standardized biotinylated primers PGMY09/PGMY11 in a TC9700 thermocycler initially set a 95°C for 9 minutes, then at 95°C for 40 cycles of one minute, 1 minute at 55°C, and 1 minute at 72°C. Amplification will be completed by an extension step of 5 minutes at 72°C. The amplified products or amplicons will next be detected by a mix of digoxigenin-labeled probes, which will enable detection of genital genotypes without specifying the implicated type(s). The digoxigenin-labeled probe will be synthesized by amplification of certain HPV types with specific probes as previously described(71). Of note, ALL genital types can be detected with these probes, including those which are not used to synthesize the probes. The detection of the generic hybridized probes with the amplicons will be performed in 96 well microplates with standardized commercial reagents of the commercial kit PCR-ELISA DIG Detection kit (Roche Molecular Biochemicals, Indianapolis, IN) using the manufacturer's protocol and incorporating the modifications suggested and published by our team(70). These modifications include: hybridization of 20 ul of denatured amplicons with a generic probe in a 200ul hybridization solution for 3 hours at 42°C. A specimen will be considered positive if the absorption measured at A405 is  $\geq 0.2$  and negative if it is  $< 0.2$ .

Specimens positive with the generic test will be submitted to a coamplification with  $\beta$ -globin specific primers and PGMY09/PGMY11 standardized primers in a TC9700 thermocycler initially set a 95°C for 9 minutes, then at 95°C for 40 cycles of one minute, 1 minute at 55°C, and 1 minute at 72°C(72–74). Amplification will be completed by an extension step of 5 minutes at 72°C. Genotyping will be performed by a reverse hybridization reaction of the biotinylated amplicons generated by the prior reaction with probes fixed on a strip (called « array ») and revealed by a colorimetric reaction. We have successfully participated to an international quality control test organized by the World Health Organisation (WHO) on HPV genotyping. Genotyping of the 36 genotypes includes types: 6, 11, 16, 18, 26, 31, 33, 34, 35, 39, 40, 42, 44, 45, 51, 52 (cross-reacting probes), 53, 54, 56, 58, 59, 61, 62, 66, 67, 68, 69, 70, 71, 72, 73, 81, 82 (two variants including IS39), 83, 84 and 89. Samples positive with the probe used for detection of type 52 and also reacting with the probe of types 33, 35 or 58 will be analyzed with a specific probe for type 52 in real time PCR because linear array's HPV-52 probe also react with types 33, 35 and 58(75).

Samples negative for these genotypes and  $\beta$ -globin positive will be considered HPV negative. Samples negative for HPV and  $\beta$ -globin will be considered inadequate for PCR.

### **3.5.3 Secondary outcomes: definition and measurement**

#### **a) Immunogenicity:**

A sub-sample of girls will be assigned to the part of the study measuring the immunogenicity and comparing seropositivity and antibody geometric mean titers (for HPV types 6, 11, 16, 18) in the two study groups.

The first 500 participants recruited will participate to the immunogenicity section of the study (250 per group). A blood sample will be collected at month 60, 90 and 120 following the beginning of vaccination in these participants. Five milliliters of blood will be collected in an 8.5 ml marbled-tube. Only 350 participants will have a blood sample at month 90.

A non-competitive serologic Luminex platform developed by the Quebec public health laboratory (Laboratoire de santé publique du Québec, LSPQ) will be used to detect and quantify HPV types' specific antibodies. This test is sensitive, replicable and quite simple to use(76,77). Depending of

the availability of the LSPQ Luminex platform, laboratory assays could be performed at the Centers for Disease Control and Prevention (CDC, Atlanta, USA) using multiplex direct IgG ELISA to HPV L1+L2 virus-like particles (VLPs) on Meso Scale Discovery platform as previously described with minor modification(78).

Clinical samples from the Vaccine Research Team CHU de Québec-Université Laval biobank (Nagano project #B12-06-986) will be used by the Frederick National Laboratory for Cancer Research (NIH/CDC) for the "9v HPV seronegatives to harmonize threshold" project to develop and validate HPV serological tests.

b) Primary outcome up to 13 years

HPV-16 and HPV-18 infections that persist at least 6 months will be measured, and this, up to **13 years** following the first injection as defined in 3.5.2.

c) Immunogenicity for 5 other types:

A sub-sample of girls will be assigned to the part of the study measuring the immunogenicity and comparing seropositivity and antibody geometric mean titers (for HPV types 6, 11, 16, 18 **and 31, 33, 45, 52, 58**) in the two study groups.

d) Condylomas:

Every year, the girls will be asked (via an online questionnaire) if a health professional told them they had condylomas. If the answer is yes, we will collect information (via a phone call by a research nurse) on the type and number of treatment(s) performed. Condylomas are not a reportable disease, it is therefore impossible to obtain information from registries. There is neither a specific claim code enabling us to collect this information via the Quebec health insurance database.

e) Comparison with retrospective cohorts of unvaccinated girls

Estimates of HPV 16 and HPV 18 persistent infections, will be obtained for various similar cohorts assembled before the beginning of vaccination in order to compared their rates to those obtained in ICI-VPH (see section on primary analysis). The same definition of persistent infection (as detailed in section 3.5.2) will be used.

### **3.5.4 Sample preservation and storage**

#### **Vaginal self-samples**

The specimens obtained with the self-samplings will be kept at a 4°C temperature. The samples will then be frozen and kept in the laboratory for 15 years. They could be tested in other HPV studies. No test on the participants' genetic profile will be performed using these samples.

#### **Sera**

The samples will be kept frozen at the research sites and during transportation to the Quebec public health laboratory (LSPQ) or the CDC laboratory for analyses.

The serum samples will be kept for 15 years. On the consent form, participants can agree to have their sample tested to identify antibodies against other vaccine preventable diseases. No genetic tests will be performed on these samples.

Study data will be kept for 25 years, after which they will be destroyed.

### 3.6 Randomization

Randomization will be performed via a web service. It will be stratified by centre (Montréal, Saguenay-Lac-St-Jean and Quebec City). Blocks varying in size between 4 and 8 participants will be used within each stratum.

### 3.7 Bias protection

We have chosen not to administer placebo to the girls randomized to the «2 dose» group for many reasons.

First, given that it is primarily an evaluation of the vaccination program, we want to perform an evaluation as close as possible to the real world environment. The girls will know if they received 2 or 3 doses whether or not the 3rd dose at 60 months is offered as part of the Quebec program. The only way through which knowledge of the number of doses received can influence the primary outcome is if it modifies the sexual behavior. Some people were worried about the fact that vaccination against STI could lead to more risky sexual behaviour, resulting from a false sense of security. Fortunately, the data available today do not support this hypothesis(79–81).

The main outcome is the detection of a virus in cervical secretions; it is therefore quite unlikely that the knowledge of the study group can influence that in anyway. The professionals in charge of the laboratory tests will not have access to the participants' randomization group. Similarly, the persons that will analyze potential screenings test will not know the group to which the participants were assigned.

Taking into consideration the related costs, risks, and inconvenience (discomfort, side effects associated to injecting a placebo) and its very low utility in improving the validity of the study results; it did not seem ethical or useful to us to include a placebo for the control group. The primary outcome will be measurement of persistent infections and completion of annual questionnaires enabling us to control for sexual behaviors in the analysis.

### 3.8 Sample size and feasibility of enrolment and follow-up.

#### 3.8.1 Sample size needed to answer the primary research question.

The sample size was calculated to test the primary hypothesis of non-inferiority of a schedule with 2 doses administered 6 months apart, compared to a 3-dose schedule (0, 6, 60 months). We fixed the power at 90% as recommended for non-inferiority trials(63). The calculations were based on a bilateral log rank test with alpha set at 0.05 (corresponding to an alpha of 0.025 for a unilateral non-inferiority test) which is close to a test based on a 95% confidence interval derived from a Cox model. The non-inferiority margin will be fixed at 5%. Based on the data available in multicentric clinical trials measuring the efficacy of a schedule with 3 closely administered doses, the cumulative incidence of persistent infections was assumed to vary from 10% to 20%(23,82) during a 5-year period and the efficacy of the 2-dose schedule is expected to vary from 91 to 95%(21,30,83). The long term efficacy of the 3-dose schedule is unknown but was evaluated at 95%, which corresponds to an annual cumulative incidence of persistent infections of 0.5 to 1% among vaccinated girls (Table 1). The 2-dose schedule could therefore be declared non-inferior if we observed a cumulative incidence of persistent infections of 1 to 2%. Table 1 summarizes the various scenarios that were evaluated to calculate the sample size.

In other words, if we agree to lose a maximum of 5% of the vaccine efficacy (VE) with a 2-dose schedule, in order to conclude that it is non-inferior, we would agree to have a  $VE \geq 90\%$  for the 2-dose schedule. Therefore with a rate of 10%, 15% and 20% of persistent infections in the absence

of vaccination, we estimate to respectively observe a rate of 0.5%, 0.75% and 1% of persistent infections in the group vaccinated with 3 doses and a non-inferiority accepting a maximum of 5, 8 and 10 persistent infections per 1000 participant among the group vaccinated with 2 doses.

We had initially set the sample size at 2,167 per group. Given an expected frequency of 25% of losses to follow-up during the study, this number will be close to an effective sample size of 1625 per group ( $2\,167 \times 0.75$ ). We believe that this sample size is close to that obtained with the most likely assumptions a 94-95% efficacy for the 2-dose schedule and a cumulative incidence of 10-15% of persistent infections (in the absence of vaccination) during the whole study. The results obtained will regularly be compared to the initial hypotheses. According to the conclusions of this comparison, the expected statistical power will be re-calculated. Adjustments on the number of participants to recruit or on the duration of follow up could be considered depending on the funding available.

**Table 1 : Sample size needed in each group for a power of 90%**

|                               | Baseline rate pf persistent infections |               |                   |                |                |                   |             |               |                   |
|-------------------------------|----------------------------------------|---------------|-------------------|----------------|----------------|-------------------|-------------|---------------|-------------------|
|                               | 10%                                    |               |                   | 15%            |                |                   | 20%         |               |                   |
| Definition of non-inferiority | 3-dose Eff                             | 2-dose Eff    | Size of the group | 3-dose Eff     | 2-dose Eff     | Size of the group | 3-dose Eff  | 2-dose Eff    | Size of the group |
| 95% to 90%                    | 95%
(0.5%)                          | 95%
(0.5%) | 1291              | 95%
(0.75%) | 95%
(0.75%) | 858               | 95%
(1%) | 95%
(1%)   | 641               |
|                               |                                        | 94%
(0.6%) | 2156              |                | 94%
(0.9%)  | 1431              |             | 94%
(1.2%) | 1070              |
|                               |                                        | 93%
(0.7%) | 4066              |                | 93%
(1.05%) | 2699              |             | 93%
(1.4%) | 2015              |
|                               |                                        | 92%
(0.8%) | 9649              |                | 92%
(1.2%)  | 6403              |             | 92%
(1.6%) | 4780              |
|                               |                                        | 91%
(0.9%) | 40525             |                | 91%
(1.35%) | 26886             |             | 91%
(1.8%) | 20067             |

\* Values in red represent the expected cumulative incidence of persistent infection in each scenario.

#### Revision of the sample size in January 2016:

We have reviewed the data used in our initial calculation and we have tried to refine and update them according to the most recent data in the literature, and what was observed in the present study after 2.5 years of activity. The modifications and precisions are on 2 aspects:

1. Estimation of the cumulative incidence of persistent HPV 16 and HPV 18 infections **per age range**, in order to more precisely evaluate the benefits and costs resulting from **following less participants for a longer period** (1 additional sample corresponding to 6 additional months of follow up, 2 additional samples corresponding to 1 year of additional follow up, etc.)
2. The proportion of losses to follow-up was reduced given the data observed in the study after following the 1st group of recruited participants for 2.5 years.
3. Proposal to adjust the budget according to the various scenarios, the various numbers of participants to be recruited and followed up and the various follow-up times.

When updating the literature search(84), we have refined our estimation of the cumulative incidence of persistent HPV 16 and HPV 18 infections per age range. Also, we have evaluated that it will be better to recruit less participants and follow them for a longer period while keeping the same study hypotheses and desired statistical power.

Table 2 presents the cumulative incidence of persistent infections that it will be possible to achieve if the participants are followed up for a longer period. It helps to calculate the number of participants needed to keep the same statistical power.

Using the values observed after 2.5 years of follow up, the percentage of losses to follow up was reviewed and set at 0% during the year of enrolment, 1%, 2%, 3% and 4% for the next 4 years respectively and 5% as of the 5th year of follow up (Table 2). We will no longer apply a global percentage of 25% of losses to follow up at the end of the study.

To meet the primary objective of the study while keeping the same hypotheses (i.e. a 95% efficacy in the 3-dose group and a 94% efficacy in the 2-dose group) the sample size needed has been calculated for follow-ups varying from 5 to 10 years corresponding to a cumulative incidence of persistent infections of 15% to 39%. When applying the percentage of losses to follow up accrued since the 1st year of participation, the number of girls to be recruited has been recalculated (Table 3).

In other words, when considering the cumulative incidence of persistent infections per age and the revised percentage of losses to follow up, for a 95% efficacy in the 3-dose group, a 94% efficacy in the 2-dose group and the enrolment of 2420 girls per group with a 4-year follow up, we will have 23 persistent infections, the same number of persistent infections that could be achieved by recruiting 1667 girls per group with a 5-year follow up or 1372 girls with a 6-year follow up.

We will therefore try to recruit 3334 (1667 X 2) participants and maintain a 5-year follow up for all of them. If this objective could not be achieved even with an additional year of enrolment, we will consider an additional follow-up of 6 months or 1 year depending on the number recruited.

Update, August 20, 2018: we recruited and randomised 3364 participants. Recruitment completed.

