**Table 2. Estimated cumulative incidence of HPV16/18 persistent infections according to the participant's age**

| Follow up (years) | Age (years) | Cumulative incidence of HPV16/18 persistent infections (%) |
|-------------------|-------------|------------------------------------------------------------|
| 0                 | 15          | 0,09                                                       |
| 1                 | 16          | 1,48                                                       |
| 2                 | 17          | 3,41                                                       |
| 3                 | 18          | 6,10                                                       |
| 4                 | 19          | 9,83                                                       |
| 5          | 20   | 15,02                                                      |
| 5,5        | 20,5 | 17,62                                                      |
| 6          | 21   | 20,21                                                      |
| 6,5        | 21,5 | 22,81                                                      |
| 7          | 22   | 25,40                                                      |
| 8                 | 23          | 30,68                                                      |
| 9                 | 24          | 35,95                                                      |
| 10                | 25          | 39,68                                                      |

**Table 3. Sample size needed per group for a statistical power of 90% and number of participants to be recruited depending of the duration of follow up (participant's age), cumulative incidence of persistent infections per age and losses to follow up per year of follow up.**

| Follow-up  | Age         | Cumulative incidence of HPV16/18 persistent infections (%) | Losses to follow-up (%) | Effective sample size (per group) | Number of participants to be recruited (per group) |
|------------|-------------|------------------------------------------------------------|-------------------------|-----------------------------------|----------------------------------------------------|
| 0          | 15          | 0,09                                                       | 0                       |                                   |                                                    |

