#### 3.8.4 Feasibility of enrolment and follow-up.

Every year, about 8,000 girls are vaccinated with 2 doses of HPV vaccine in the two main health regions (Montreal and Capitale-Nationale [Quebec city region]). We plan to increase the radius of enrolment to neighboring towns and towns in the vicinity (using the area covered by the CLSC of residence and postal codes) of the two research centres (e.g. Laval, Montérégie, Chaudières-Appalaches, Saguenay-Lac-Saint-Jean). This will enable an increase of the number girls that could be invited to participate. Enrolment will be done over 4 years. By inviting all the girls in a cohort (e.g. the first cohort will be those vaccinated in 2008-2009) with a 10% participation rate ( $14\,500 \times 0.10 = 1\,450$ ), we will be able to achieve our enrolment objective. According to the assumptions detailed in section 3.8.1, and in order to fulfill our objective, we will have to accrue between 22 and 52 persistent infections. We will have to follow-up each cohort for a minimum of 5 years in order to accrue this number of outcomes.

Many strategies implemented in these studies to maintain the children's participation to the study will be repeated here (e.g. identifying more than one postal address and more than one phone number, sending SMS yearly, etc.). We will equally ask the participants' authorization to obtain their contact information from the Quebec health Insurance Board in case we have difficulties getting in touch with them.

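### The stated 90% power does not match the plan's own 23 expected events: at the sizing margin (hazard ratio 2.0) it needs about 161, and 23 give about 23% power

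*Protocol*

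**What the plan says.** Section 3.8.1 sets the design target: "We fixed the power at 90% as recommended for non-inferiority trials". The calculation is a "bilateral log rank test with alpha set at 0.05 (corresponding to an alpha of 0.025 for a unilateral non-inferiority test". The margin is described through vaccine efficacy (VE): with 95% for three doses, "we would agree to have a $VE \geq 90\%$ for the 2-dose schedule".

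The unvaccinated incidence is taken as 10% to 20% over five years. Applying 95% efficacy gives a figure "which corresponds to an annual cumulative incidence of persistent infections of 0.5 to 1% among vaccinated girls". The note under Table 1 calls the same values expected cumulative incidences, and the paragraph before the table speaks of 10 to 15% over the whole study.

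The January 2016 revision keeps the hypotheses (95% against 94%). Table 2 gives an unvaccinated cumulative incidence of 15.02% at five years. Table 3, headed "Sample size needed per group for a statistical power of 90" percent, gives 1431 effective and 1667 recruited per group for five years of follow-up. The text says that "we will have 23 persistent infections, the same number of persistent infections that could be achieved by recruiting 1667 girls per group" for five years. Section 3.8.4 adds that "we will have to accrue between 22 and 52 persistent infections". The August 2018 update reports 3364 randomised.

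**The concern.** Five percent of a five-year risk is still a five-year risk, so the word *annual* in section 3.8.1 conflicts with the sentence it sits in. More importantly, the revision states both an event count and a power. In a log-rank design the power follows from the events, the margin and the true hazard ratio, so the two can be checked against each other, and 23 events look far too few for 90%.

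This bears on the primary objective. Section 5 attaches a consequence to non-inferiority not being shown (a third dose is offered to the two-dose group), and section 3.8.1 promises to recalculate power against observed results. Both rest on a starting power that the design does not have.

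**Working it through.** **Inputs.** One-sided alpha 0.025 and power 90% (section 3.8.1), so (1.960 + 1.2816)² = 10.507. Margin: VE 95% to 90%, that is risk from 5% to 10% of baseline, hazard ratio (HR) 2.0. True HR: 1.0 for VE 95% on two doses, 6%/5% = 1.2 for 94%, 7%/5% = 1.4 for 93%. Incidences and yearly losses are from Tables 2 and 3.

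**1. Reproducing the plan's sizes.** Take the Table 1 cell with 15% baseline, 94% against 95% (stated 1431).
- Freedman's formula, margin arm (1.5%) against two-dose arm (0.9%), risks treated as *yearly* over five years: survival 0.985⁵ = 0.9272 and 0.991⁵ = 0.9558; hazard ratio 1.672; events 10.507 × (2.672/0.672)² ≈ 166; N = 166.2/(2 − 0.9272 − 0.9558) ≈ 1421. All 15 cells of Table 1 fall within 1.6% and all nine rows of Table 3 within 2%.
- Schoenfeld's formula with yearly hazards, 4-year accrual plus 5-year follow-up, also fits: 1272, 2134, 856, 1437, 648 against the stated 1291, 2156, 858, 1431, 641.
- The same risks counted once, as cumulative, do not fit: Freedman 6926, Schoenfeld 9762.

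**2. Events the plan expects.** Effective N × incidence × (0.05 + 0.06): 1431 × 0.1502 × 0.11 = 23.6. The four-year row gives 2186 × 0.0983 × 0.11 = 23.6, and every other row of Table 3 also gives 23.6. This agrees with the plan's 23. So the events count the risk once, while the sample sizes accumulate it again.

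**3. Events that 90% power needs.** D = 4 × 10.507/[ln(2/HR)]².

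| Two-dose VE | True HR | Events needed |
|---|---|---|
| 95% | 1.0 | 87 |
| 94% | 1.2 | 161 |
| 93% | 1.4 | 330 |

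For 15% baseline and HR 1.2, 161.07/(0.15 × 0.11) ≈ 9,762 evaluable per group, 6.8 times the stated 1431.

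**4. Power with the planned events.** Power = Φ(½√D × ln(2/HR) − 1.96).
- 23 events, HR 1.2: 23%. A simulation with 1431 per group gives 23.6%.
- HR 1: 38% with 23 events. With the 1431 × 0.1502 × 0.10 = 21.5 events that equal efficacy would produce, 36%.
- An observed HR of exactly 1.0 on 23 events has an upper 95% limit of exp(1.96 × 2/√23) = 2.26, above 2.0.

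**5. For the 3364 randomised (1682 per group), five years.** Retention is 0.99 × 0.98 × 0.97 × 0.96 × 0.95 = 0.858.
- Final retention × final incidence: 1682 × 0.858 × 0.1502 × 0.11 = 23.9 events (HR 1.2) and, with factor 0.10, 21.7 (HR 1). Power 24% and 36%.
- Counting events before dropout, losses assumed mid-year: the yearly increments of Table 2 after year 0 (1.39, 1.93, 2.69, 3.73, 5.19 points) times mean retention (0.995, 0.980, 0.956, 0.922, 0.881) sum to 13.86%. That gives 25.6 and 23.3 events, power 25% and 39%.

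**6. Follow-up to 2021.** With four equal cohorts followed 5, 6, 7 and 8 years, and every retained participant accepting the extension, the same two methods give 33 to 37 events and 31 to 35% power at HR 1.2, and 30 to 34 events and 48 to 52% at HR 1.

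**7. Losses in Table 3.** The 5.5-year row is 1220/(0.858 × 0.95) = 1496, and the 6-year row is 1063/(0.858 × 0.95²) = 1372. A yearly 5% is charged at each half-year step up to seven years, and the later rows inherit the excess.

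**The case against.** - **The cause is not documented.** Two different yearly-rate calculations fit Table 1 about equally well, so the method actually used is unknown. This stands: the slip from cumulative to yearly is an inference, supported by the word *annual*. The shortfall does not depend on it, because the plan states the events itself.
- **The range of 22 to 52 may be a forecast, not a requirement.** It matches the earlier size of 2167 per group: 2167 × 0.10 × 0.10 = 21.7 and 2167 × 0.20 × 0.12 = 52.0. That is a plausible origin, but section 3.8.4 presents it as what must be accrued. Even 52 events give only 45% (HR 1.2) or 71% (HR 1).
- **An absolute margin might have been meant.** The plan names a log-rank test and a Cox model. A risk-difference margin of 0.75 points would need 4,776 per group, and 1431 would give 43% or, at equal efficacy, 64%.
- **The extension and the promised power review may help.** They help somewhat, but do not restore 90%. Follow-up beyond ten years from the first injection belongs to secondary objective 2.2b, not to the primary objective.
- **A reader might infer that the trial will probably be inconclusive even if the schedules are equal, and that failure would be misread as evidence against two doses.** The first is too strong once the extension is counted, when power is close to even at equal efficacy. Nothing in the protocol supports the second.

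**Conclusion.** The stated 90% power is wrong. At the margin used for sizing, the five-year design has about 23 to 25% power at 94% against 95% efficacy and about 36 to 39% at equal efficacy. The plan expects about 23 events where it needs about 161 or 87.

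These figures rest on HR margin 2.0, one-sided alpha 0.025, Table 2's incidences and the plan's loss rates. Section 3.9 instead sets the limit for the hazard ratio at 1.05. Under that rule power is far lower still: about 3% with 24 events at true HR 1, and 90% power would need about 17,700 events. The two margins are a separate contradiction, but no power statement is complete until it is settled.

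**What to change.** No new enrolment is called for.

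1. In section 3.8.1, delete *annual* and state one time base for every incidence.
2. Correct the sizes in Tables 1 and 3, or replace their 90% claim. For 3364 randomised and five years of follow-up, state about 24 to 26 events and 24 to 25% power at 94% against 95% efficacy, and about 22 to 23 events and 36 to 39% at equal efficacy. Say that the lower values apply the plan's retention to the final incidence, and that the upper values count events before dropout with losses assumed mid-year.
3. Give power with follow-up to 2021 separately, under objective 2.2b: about 31 to 35% and 48 to 52%, with the cohort and acceptance assumptions stated.
4. In section 3.8.4, replace the range of 22 to 52 by the events needed for 90% power: about 87, 161 and 330 for two-dose VE of 95%, 94% and 93%.
5. Recompute the losses in Table 3 from 5.5 years upward.
6. State that all these figures assume HR margin 2.0, and reconcile that margin with the 1.05 in section 3.9 before the figures are inserted.

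The cost is protocol wording and a much less favourable stated power.
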